**Figure 2 F2:**
[figure not shown]
**Flowchart Hepatitis B screening in Turkish Dutch**.

### Follow-up measurements

If test results have not been received by the MPHS four weeks after the laboratory form request, participants who have indicated to wish to be reminded of the testing, are sent a reminder email. Five weeks after the first log-in, participants who provided an email-address and have given consent for being approached for further research, will receive an email with a link to the website where a short questionnaire on social-cognitive and socio-cultural determinants, and the perceived quality of the intervention is presented. After completion of the questionnaire, participants may indicate whether they want to join in a raffle (based on email-addresses) of gift vouchers, as a token of appreciation for their participation.

### Sample size

The size of the total first generation Turkish population in Rotterdam aged 16-40 years is approximately 10,000. We expect that after having received the letter, approximately 60% of this population will go to the website (n = 6000, i.e. 2000 visitors in each group), and that half of that group will receive a test-advice and laboratory form (n = 3000, 1000 in each arm of the study). We hypothesize that in the three groups (standard information, individually tailored information and cultural tailored information) 20%, 35% and 45%, respectively, will go to the test location and be tested for HBV (n = 200, n = 350, n = 450, respectively). Accordingly, power calculations for the difference in compliance with the advice between the tailored and cultural tailored group, show a power of more than 0.90. Because of clustering in families (we randomize by house address), we take into account the effect of the cluster 'family', which may affect the power. Therefore we take a power of 0.90 as acceptable instead of the standard 0.80. Our hypothesis would lead to a total of 1000 tested persons, approximately 10% of the total target population. Based on responses in other studies, we expect that this predicts the actual response reasonably well [31-34].

### Measures

During the intervention, we will gather the following information:

Demographic factors: gender, age, socio-economic status (SES) of the residential area (categorized in low-mid/high SES by postal code), marital status, level of education (low-medium-high), income situation, type of health insurance, religion, and whether the person knows someone with HBV.

Social-cognitive factors: awareness, knowledge, attitude, self-efficacy, perceived subjective norm and support, susceptibility to HBV, personal norms related to health and the screening intention.

Socio-cultural factors: satisfaction with the Dutch health care and perceived rules regarding health and disease.

### Primary outcome measure

The primary outcome variable is having been tested due to the intervention (yes/no). The data will be available from the client registration system from the MPHS.

### Secondary outcome measures

The follow-up questionnaire will provide information on secondary outcomes by measuring the change in the following determinants one month after logging in on the website:

Awareness: In the past three months, did you think about a hepatitis B test? Answering options: never heard of a HBV-test, never thought of a HBV-test, heard of a HBV-test but not decided, heard of a HBV-test and decided (not) to take it, have had a HBV-test. The measure was based on the Precaution Adoption Process Model (PAPM) [35] and adapted from Costanza [36]. The awareness score may range from 0 to 5.

Knowledge is measured by five statements in order to provide tailored information about the most important issues of HBV for this population. The items were on the contagiousness of HBV, the main route of transmission in Turks, the occurrence in Turks, the serious consequences of HBV and the prevention of HBV. The knowledge score may range from 0-5.

Attitude is measured by six items about three pro's (each may score 1 point) and three con's (each may score -1) of HBV testing. The attitude score may range from -3 to 3.

Self-efficacy is measured by 4 items (on a scale from 1-10) about the ability to discuss testing with parents and/or partner, the ability to communicate with a doctor about the test, and to arrange testing.

Subjective norm is measured by asking whether the participant thinks parents and/or partner feels testing is important (scale 1-10).

Social support is measured by multiplying the scores on two questions: 1.) whether the participant thinks parents and/or partner will support the participant in testing (yes (1)/no (-1)), and 2.) whether this is important for the participant (yes (1)/no (0)). The score may range from -1 (negative support) to 1 (positive support).

Susceptibility to HBV is measured by asking the participant to indicate how susceptible he/she feels regarding HBV, and to ask how he rates his susceptibility related to other inhabitants of the Netherlands. Both items are measured on a 10 point scale (very low chance, very high chance).

Personal norm is measured by two items 'I should care well for my own health' and 'I am responsible for the health of others' on a five point scale (agree (1) - disagree (5)).

Perceived rules is measured by asking persons who indicated to be religious whether they perceive rules in their religious community about: how to deal with health, how to prevent disease, being responsible for one's own health/the health of others. Answers may be yes (1) or no (0), which may result in a rules-score of 0-4.

Satisfaction with Dutch health care is measured on a five-point scale by three statements on the cost of health care, the experience of doctors, and satisfaction with the Dutch health care in general.

Screening intention is measured on a five-point scale by asking whether the participant intends to be tested within three months (for sure (5) - surely not (1)).

### Analysis

Because the primary outcome variable is the percentage of eligible persons having been tested due to the intervention (yes/no), we will perform univariate and multivariate logistic regression analysis. Independent variables that will be included in the regression analysis are the demographic, social-cognitive and socio-cultural factors.

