Tailoring is defined as any combination of information or change strategies intended to reach one specific person, based on characteristics that are unique to that person, related to the outcome of interest, and have been derived from an individual assessment [29]. The individually tailored intervention focuses on social-cognitive determinants of screening behaviour, such as awareness, knowledge, attitude, self-efficacy, perceived subjective norm and support, susceptibility to HBV, and personal norms related to health. Cultural tailoring may be defined as tailoring a health message 'which recognizes and reinforces a group's cultural values, beliefs, and behaviours and built upon those to provide context and meaning to the message about a given health problem or behaviour' [25]. Cultural tailoring is expected to have even more impact on behaviour than tailoring, by paying attention to the embeddedness of human health behaviour in the cultural context and social structure [30]. Cultural sensitivity in tailoring can be conceptualized in terms of two primary dimensions: surface structure and deep structure [25]. We used surface structure elements in order to increase the comprehension and acceptance of messages, by matching intervention materials and messages to characteristics of the target population, such as the language and role models preferred by the target audience. We used deep structure elements to convey salience, by understanding how members of the priority population perceive the cause, course, and treatment of hepatitis B, as well as how they perceive the determinants of the desired screening behaviour. We addressed factors such as religion and family values that influence screening behaviour. A detailed description of the intervention is described elsewhere ([name]: Development of a culturally tailored internet intervention promoting hepatitis B screening in the Turkish Dutch community, submitted).

This study aims to evaluate the effectiveness of the two tailored internet interventions as compared to generic online information on HBV, and to assess the added value of additional tailoring on socio-cultural factors.

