## Methods/Design

### Study design

We apply a cluster randomised controlled trial to study the effect of the individually tailored internet intervention (group B) and the culturally tailored internet intervention (group C) on screening behaviour, compared to generic online information (group A). Measurements of screening behaviour (i.e. being screened for HBV (yes/no)) and of the determinants of this behaviour will be at baseline and one month post-intervention.

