## Discussion

This trial will determine the effectiveness of a cultural tailored internet intervention promoting HBV-screening in first generation Turkish immigrants, aged 16-40 years, living in Rotterdam.

It is difficult to estimate the expected response rate because this study is the first in this population using a culturally tailored internet approach. In order to generate sufficient power to show the value of the individually tailored and the culturally tailored intervention, we will need at least 1000 participants, 10% of the total target population. Regular public health interventions such as PAP smear testing for cervical cancer, show response rates in the range of 49.8% to 67.7% in Turkish immigrants in the Netherlands, with invitations from general practitioners having a higher response compared to invitations from the MPHS [38]. In a community project in which individuals were invited to be tested for hepatitis B (by mail for a personal consultation at the community centre), the response among the Turkish population was 26% [31]. A recently introduced Chlamydia screening programme in 16-29 year-old inhabitants of three area's in the Netherlands also used a combination of a personal invitation by post and the option to request a test package through the internet. This resulted in a response of 16% in the general population [33]. An important factor in motivating the invited people to participate might be the endorsement of our project by community leaders. We therefore have asked for the advice of community leaders in the development phase of the project. We also plan to specifically address community leaders and community-based organisations during the information campaign in the Turkish community in Rotterdam, using community-based organisations and key figures in the Turkish community. However, it remains to be seen whether the members of the target community that are involved, sufficiently represent their community in order to facilitate implementation of the intervention. Furthermore, next to the primary outcome (having been tested or not) it is important to learn from possible changes in social-cognitive and socio-cultural determinants related to HBV-screening. It has recently been shown that follow-up questionnaires have high drop-out rates [39]. The raffle of gift vouchers may help motivate people to fill out the questionnaire.

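### The stated primary regression does not list randomised group among its independent variables, so as written it estimates none of the trial's three comparisons

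*Protocol article*

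**What the plan says.** The aim at the end of the Background is "to evaluate the effectiveness of the two tailored internet interventions as compared to generic online information on HBV, and to assess the added value" of the extra cultural layer. That gives three contrasts on one binary outcome: B vs A, C vs A and C vs B. The Abstract gives the same three. The Study design section describes only B and C set against A. The Sample size section assumes that "20%, 35% and 45%, respectively, will go to the test location and be tested for HBV" in groups A, B and C, and reports that "power calculations for the difference in compliance with the advice between the tailored and cultural tailored group, show a power of more than 0.90", which is C vs B.

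The Analysis section has two sentences. The first names univariate and multivariate logistic regression for the primary outcome. The second gives the model terms: "Independent variables that will be included in the regression analysis are the demographic, social-cognitive and socio-cultural factors". These are the three families of variables defined under Measures, and none of them contains the allocated group. No other section says that group enters the model.

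**The concern.** A randomised comparison needs a term for the randomised group. A regression on participant characteristics alone shows who tends to be tested. That is useful for describing determinants, but it says nothing about whether a tailored site raises testing. An analyst who followed the sentence exactly could not answer the trial's question. An analyst who added group on their own initiative would be choosing the contrasts and covariates of the primary analysis without guidance from the text.

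A second matter follows once group is in the model: three arms allow three pairwise tests, and the article does not say how each will support a claim.

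**Working it through.** **1. What the listed model can estimate.** Write X for the three listed families of variables. The model is logit P(tested) = b0 + b'X. Two people with the same X have the same predicted probability whether they were allocated to A, B or C, so no coefficient corresponds to an arm contrast.

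At the planning figures (Sample size: "n = 3000, 1000 in each arm of the study"; 20%, 35%, 45%), the quantities with no term are:

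- B vs A: (0.35/0.65)/(0.20/0.80) = 0.538/0.250 = odds ratio 2.15
- C vs A: (0.45/0.55)/(0.20/0.80) = 0.818/0.250 = odds ratio 3.27
- C vs B: 0.818/0.538 = odds ratio 1.52

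If X is taken at baseline, randomisation balances it across arms on average. The model would then predict about the same rate in every arm: (200 + 350 + 450)/3000 = 33.3%, against assumed rates of 20%, 35% and 45%.

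**2. The plan's own power figure.** For C vs B with 1000 per arm, ignoring clustering and assuming two-sided 5% (no level is stated), the pooled rate is 0.40:

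- Standard error under no difference: sqrt(2 × 0.40 × 0.60/1000) = 0.02191
- Standard error under the alternative: sqrt((0.35 × 0.65 + 0.45 × 0.55)/1000) = 0.02179
- Power = Φ((0.10 − 1.96 × 0.02191)/0.02179) = Φ(2.618) = 0.996

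The stated power of more than 0.90 is reproduced. With assumed design effects of 1.2, 1.5, 1.8 and 2.0 for household clustering it becomes 0.99, 0.96, 0.93 and 0.90. The article gives no design effect.

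**3. Family-wise error, conditional on assumptions the article does not make.** Suppose the arms do not differ, each pairwise test is a valid two-sided 5% test, and any significant result counts as success.

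- All three pairs: P(range of three standard normals > 1.96 × √2) = 0.122. Simulated trials with 1000 per arm gave 0.122 to 0.123.
- Only B vs A and C vs A (test statistics correlated 0.5): 0.091.

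**4. A global test first.** With three arms, if any two pairwise null hypotheses are true, all three arms are equal. The only intersection to test is therefore the global one. A two-degree-of-freedom test at 5%, followed by each pair at 5%, is a closed procedure. In simulation the family-wise error was 0.049 to 0.050, and C vs B power at 35% vs 45% stayed at 0.996. Bonferroni over three tests gives 0.985 by the formula in step 2 with level 0.05/3.

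**The case against.** The strongest defence is that the intent is plain. The primary outcome is defined as testing that results from the intervention, and the Study design section says that B and C are compared with A. The sentence in the Analysis section can be read as a covariate list with the obvious exposure left unsaid, in an article that condenses a fuller protocol. As an account of what the authors meant, this is probably right. It does not repair the text, because the sentence says which independent variables will be included and group is not one of them.

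Three stronger readings are tempting, and the article does not support them.

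- *The sections contradict each other about the contrast.* They do not. The Abstract and Background name all three contrasts consistently, and the Study design section gives a subset. The Sample size section powers C vs B, the smallest assumed difference (10 points, against 15 and 25), which is ordinary practice when several contrasts matter.
- *The trial carries a 12% false-positive rate.* The article states no significance level, does not say that three tests will be run, and does not say that any one counts as success. Such rules may lie in an analysis plan not shown here, so silence on them is not an error. Whether separate claims in a multi-arm trial need joint error control is also debated.
- *C could beat A but not B, so the verdicts conflict.* These answer two separately stated questions. If B and C truly have equal rates, a non-significant C vs B in 95% of trials is simply one minus the 5% level. A global test would not change that.

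**Conclusion.** The point holds for the model statement. The only specification of the primary regression omits randomised group, and followed literally it estimates none of B vs A, C vs A or C vs B. This rests on the text alone and needs no numerical assumption. The odds ratios of about 2.2, 3.3 and 1.5 show what is left out at the plan's own rates.

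It does not affect recruitment, allocation or data collection, and it is most likely a slip. It should still be corrected before analysis, because it concerns the primary result. The family-wise figures of about 12% (three pairs) and 9% (the two comparisons with A) are conditional on unstated testing rules. They support a safeguard and do not show an error in the plan.

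**What to change.** In the Analysis section:

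- Make randomised group (A/B/C) the main independent variable of the primary logistic model. Keep the listed factors only as covariates, at their baseline values, because the determinants are measured again at follow-up as secondary outcomes. Allow for clustering by house address.
- State that effectiveness against generic information is judged from B vs A and C vs A, and that the added value of cultural tailoring is judged from C vs B, the contrast behind the sample size. Name all three contrasts in the Study design section.
- As a safeguard, test group first with one two-degree-of-freedom test at two-sided 5%. If it is significant, test the three pairs, each at 5%. All of these tests should allow for clustering.

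The cost is a few sentences and one extra test, with no more participants. The one downside is that an isolated pairwise p-value just under 0.05 could not be claimed when the global test fails. At the planned rates C vs B power is unchanged.

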**Methods/Design:**

A cluster randomized controlled trial design, in which we invite all Rotterdam registered inhabitants born in Turkey, aged 16-40 (n = 10,000), to visit the intervention website is used. A cluster includes all persons living at one house address. The clusters are randomly assigned to either group A, B or C. On the website, persons eligible for testing will be selected through a series of exclusion questions and will then continue in the randomly assigned intervention group. Group A will receive generic information on HBV. Group B will receive individually tailored information related to social-cognitive determinants of screening. Group C will receive culturally tailored information which, next to social-cognitive factors, addresses cultural factors related to screening. Subsequently, participants may obtain a laboratory form, with which they can be tested free of charge at local health centres. The main outcome of the study is the percentage of eligible persons tested for HBV through to participation in one of the three groups. Measurements of the outcome behaviour and its determinants will be at baseline and five weeks post-intervention.

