### Randomisation and exposure to the intervention

All persons living at the same address (i.e. family members or house-mates), will be assigned randomly to one of the three research groups: standard information (group A), individually tailored information (group B) and culturally tailored information (group C). Participants in the control (group A) and intervention groups (groups B and C) are thus enrolled in the same way. Those who enter the internet page and show to be eligible for testing will be questioned for demographic information and asked for a current email address for participation in a follow-up questionnaire. When participants stop during the internet session, and log in using their client ID later on, they will continue in the same group.

During the intervention, participants provide information on both social-cognitive and socio-cultural determinants by answering questions on their beliefs and expectations regarding hepatitis B screening. This information and the provided demographic data will be linked to the client ID and saved in a database. At the end of the information session or tailored intervention, participants may choose to receive a laboratory form either by email or post. Prior to receiving the form, they will receive client information, in which the procedure of testing, possible results of the test and follow-up is explained. Participants will then be asked to sign a checkbox for informed consent. Participants are also asked to co-operate in a follow-up questionnaire about the website one month after the date of first website visit. The laboratory form will be either sent by email or mail, and the client information is once more included. When the participant is younger than 18 years at the date of printing the form, a signed consent from the parents is needed on the form. In that case, information for the parents will be included in the client information. For individuals unable to use the internet, we will provide the laboratory form with generic information on HBV on request by postal mail. However, these individuals are excluded from the research population, as they are not exposed to one of the three interventions.

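### The regression for the primary outcome takes in social-cognitive and socio-cultural factors without limiting them to values recorded before arm-specific content, so it may condition on mediators

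*Protocol article*

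**What the plan says.** **Model.** For the primary outcome, tested or not, the Analysis section states that "we will perform univariate and multivariate logistic regression analysis", and then: "Independent variables that will be included in the regression analysis are the demographic, social-cognitive and socio-cultural factors". It does not say at which time point these factors are taken, or which of the two regressions carries the comparison between groups.

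**Factors.** Measures lists them. The social-cognitive set runs from awareness and knowledge to screening intention. The socio-cultural set is satisfaction with Dutch health care and perceived rules on health and disease.

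**Timing.** The article describes it in two ways:
- Measures: "During the intervention, we will gather the following information". The section on randomisation and exposure: "During the intervention, participants provide information on both social-cognitive and socio-cultural determinants by answering questions on their beliefs and expectations regarding hepatitis B screening".
- Study design has measurement "of the determinants of this behaviour will be at baseline and one month post-intervention". The abstract says: "Measurements of the outcome behaviour and its determinants will be at baseline and five weeks post-intervention".

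**Role in the trial.** The Background says: "The individually tailored intervention focuses on social-cognitive determinants of screening behaviour". It adds that group C's cultural tailoring addresses socio-cultural factors as well. Secondary outcome measures makes change in the same factors, screening intention included, the secondary outcomes.

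**The concern.** One set of variables has three roles: target of the tailored arms, secondary outcome, and covariate in the model for the primary outcome. A covariate recorded before the content can act does not distort a randomised comparison. A covariate that the content has already moved is a mediator. A model that holds it fixed estimates only the part of the arm effect that bypasses it. The aim of the trial is the total effect of each website version on testing.

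The covariate sentence allows either kind of value. If later values enter and the adjusted model is read as the result, a tailored arm that works through attitude, self-efficacy or intention could be reported as having little effect.

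Values from the follow-up questionnaire would add two problems, and nothing in the sentence excludes them. One answer option of the awareness item is having had the test, which overlaps the primary outcome. The questionnaire also goes only to participants who gave an email address and consent, and the Discussion foresees high drop-out, so the model would be fitted to a selected subset.

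**Working it through.** **1. The plan's own figure.** Inputs from Sample size: 1000 per arm, 35% (B) and 45% (C), stated power above 0.90. Two-sided alpha of 0.05 is assumed, since the article gives none.

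Power = Φ{[|p₂ − p₁| − 1.96·√(2p̄(1 − p̄)/n)] / √([p₁(1 − p₁) + p₂(1 − p₂)]/n)}

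- p̄ = 0.40; √(2 × 0.40 × 0.60/1000) = 0.02191
- √((0.2275 + 0.2475)/1000) = 0.02179
- (0.10 − 1.96 × 0.02191)/0.02179 = 2.62, so power = 0.996

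The stated figure is reproduced. Covariate choice does not alter it. The unadjusted odds ratio is (0.45/0.55)/(0.35/0.65) = 1.52.

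**2. What adjustment does, by timing.** The article gives no mediated share and no strength of association between the factors and testing, so both are assumed. The simulation had 1000 replicates, 1000 per arm and independent persons. One standardised factor M stood for the determinants:

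logit P(tested) = a + d·T + 0.8·M, with M normal, mean s·T, variance 1; T = 0 for B and 1 for C.

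The intercept and total effect were set so that the marginal rates are 35% and 45%. This gives a total log odds ratio, at a given M, of 0.594 × 0.8 = 0.475, and exp(0.475) = 1.61. A share f of it runs through M: s = f × 0.475/0.8 and d = (1 − f) × 0.475. The adjusted odds ratio should therefore be close to exp[(1 − f) × 0.475]. For f = 0.5 this is exp(0.2376) = 1.27.

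| Value of M entered | Share mediated | Adjusted OR | Power, adjusted |
|---|---|---|---|
| Before exposure | none | 1.61 | 0.999 |
| After exposure | 25% | 1.43 | 0.96 |
| After exposure | 50% | 1.27 | 0.68 |
| After exposure | 75% | 1.12 | 0.21 |
| After exposure | 100% | 1.00 | 0.04 |

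The unadjusted fit gave an odds ratio of 1.51 to 1.52 and power of 0.99 or more in every row. The Monte Carlo standard error at 0.68 is √(0.68 × 0.32/1000) = 0.015.

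**3. Reading the table.** In the first row the rise from 1.52 to 1.61 is the usual non-collapsibility of the odds ratio, not bias, and no power is lost. Attenuation in the other rows is best judged against 1.61. At 25% mediated, power is still above the plan's 0.90; at 50% it is below.

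**4. Which row applies.** The article does not settle this. Study design and the abstract, with their baseline measurement, point to the first row. Measures and the randomisation section, with collection during the session, allow the others, at least for items asked after some content has been shown. The place of screening intention in the session is not stated.

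**The case against.** The strongest reply is that the in-session answers are the baseline. The only other measurement described is the follow-up questionnaire, and a change score needs an earlier value. The Background defines tailoring as resting on an individual assessment, so an answer that drives feedback must come before that feedback. Being after randomisation is also not the same as being after exposure: client IDs are allocated before the invitations go out, so everything recorded on the website, demographics included, follows randomisation. The univariate regression could supply the unadjusted group effect, and the multivariate model is nowhere called primary.

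Most of this stands. A reader might infer that the factors are mediators as a matter of fact and that the planned analysis removes the effect under test. The documents do not support that: they call for a baseline value, and harmful timing is possible but not established. A reader might also infer from the missing arm term that no arm comparison is planned. The aim and Study design state the comparison of the three groups, so the omission is more likely condensation in a short article and is not an error on its own.

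The reply does not close the gap. Preceding its own feedback does not place an item before all arm-specific content, since later questions may follow earlier messages. No sentence restricts the covariates to values before exposure, and none says which model gives the A, B and C contrasts.

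**Conclusion.** The point holds in conditional form. The one statement of the model for the primary outcome commits to covariates that the arms are built to change, leaves their timing open, and stands beside two differing descriptions of that timing. To the extent that values recorded after exposure enter, the adjusted arm coefficient is not the total effect. If all values precede the content, nothing is lost.

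The possible size runs from no loss (adjusted odds ratio 1.61, power 0.999) to complete loss (1.00 and 0.04), against an unadjusted 1.52 and about 0.99. The range rests on an assumed mediated share, an assumed log odds ratio of 0.8 per standard deviation, a single summary factor and no allowance for clustering. It illustrates the mechanism and does not predict this trial's result. Confidence is moderate. The point calls for a correction of the wording before analysis and ranks below a flaw that would undermine the trial.

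**What to change.** - **Primary test.** State it as tested (yes/no) by arm (A, B, C), accounting for address clusters, either unadjusted or adjusted only for demographics and determinant values recorded before any arm-specific content.
- **Timing.** State for each determinant, screening intention in particular, whether it is asked before, during or after that content, and bring Study design, the abstract, Measures and the randomisation section into line.
- **Other models.** Keep models with determinants recorded during or after the content, including screening intention, as separate exploratory mediation or predictor analyses.
- **Reporting.** Take the arm contrasts only from the primary model.

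The cost is wording. No new data or participants are needed, the sample size is unaffected, and the predictor analysis is kept.
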